### Intervention

The trial solution (racemic ketamine or normal saline placebo) is formulated and packaged by the manufacturer in compliance with good manufacturing practice (GMP) manufacturing and labelling standards and the Pharmaceutical Inspection Co-operation Scheme (PICS) code of medicinal manufacturing, with active drug and placebo solutions presented in identical form in individual numerically coded vials. Allocation of the correct vials to a randomised patient is controlled by the drug management module within the trial electronic database and communicated to research staff via the web-based portal after randomisation.

Patients randomised to the intervention arm are given an intraoperative loading dose of 0.5 mg/kg (capped at 100 kg body weight) ketamine, after induction of anaesthesia and prior to surgical incision. This is immediately followed by an infusion of 0.125 mg/kg/h which runs until wound closure. This relatively low infusion rate sits within the dose range where inhibition by ketamine of opioid induced hyperalgesia has been demonstrated, which is mediated by the NMDA receptor and is commonly seen in opioid use for chronic pain [20, 21]. This initial dose was chosen as the most likely to generate any potential mechanistic benefits of ketamine in inhibiting central nervous system sensitisation and chronic pain establishment, while minimising side effects. The infusion is recommenced in the post anaesthesia care unit (PACU) at the same rate and continued for up to 72 h while the patient is receiving postoperative opioid analgesia and has ongoing IV access. The placebo arm receives a loading and infusion of the placebo solution at an identical volume and infusion rate.

The pragmatic trial protocol is designed to be compatible with modern principles of early mobilisation and enhanced recovery after surgery, with cessation of the infusion where IV access and/or opioid analgesia is ceased or the patient is being prepared for hospital discharge. The infusion rate can be adjusted by escalation in response to severe or refractory acute postoperative pain (increase to 0.25 mg/kg/h) or reduction if problematic ketamine induced side effects are suspected (reduction to 0.0625 mg/kg/h with cessation after a further 6 h if clinically indicated). If, due to ongoing refractory acute postoperative pain despite dose escalation (e.g. Numerical Rating Scale (NRS) pain scores > 5/10 at rest with functional impairment of postoperative mobilisation), an open label ketamine infusion is considered necessary by the treating clinicians, this can be commenced and the trial infusion ceased, and the patient’s treatment allocation in a secondary ‘as treated’ statistical analysis will be adjusted.

Perioperative anaesthetic management is conducted at the discretion of the attending anaesthetist. Anaesthesia is induced with IV propofol, with or without opioid and neuromuscular blockade as required. Maintenance of anaesthesia is achieved with volatile agent or propofol at the anaesthetist’s discretion. Opioids and other ancillary analgesics and antiemetics including dexamethasone can be administered intraoperatively in the usual clinical manner. IV lignocaine infusion is not permitted. Postoperative oral and/or parenteral opioids are prescribed and delivered as required according to local hospital protocols. Regional or neuraxial blockade, ancillary analgesia (including NSAIDs, cyclooxygenase (COX)−1 and COX-2 inhibitors, paracetamol, tramadol, tapentadol, and gabapentinoids) can be administered according to standard practice.

Trial research staff visit the patient daily for the first 3 days or until hospital discharge, for postoperative data collection and to liaise with the treating ward staff and acute pain service to coordinate trial solution administration with the patient care plan for each day. Follow-up data collection takes place after hospital discharge, and CPSP incidence is measured at 3 months and 12 months after surgery.

### Perioperative data collection

Preoperative data relevant to the risk of CPSP, including demographics, major co-morbidities, preoperative medications, and perioperative data, are collected. A baseline EQ-5D-3L [22] is collected in all patients for measurement of quality of life along with the Kessler K-10 Psychological Distress Scale [23], and in those who report preoperative pain in the area of the surgery, the modified Brief Pain Inventory short form (mBPI-sf) [24] and Neuropathic Pain Questionnaire (NPQ) [25] are completed.

Anaesthetic technique, medications, surgery type, time and date of surgery start and completion, and trial drug administration are documented. Time to discharge from the post-anaesthesia care unit (PACU) is recorded and quality of recovery is quantified using the QoR-15 [26] on postoperative day 1.

Acute postoperative pain severity is measured using opioid and other analgesic/antihyperalgesic drug consumption, and NRS pain scores, daily for the first 3 days or until discharge from hospital (whichever is sooner). Minimum, maximum, and mean NRS pain scores at rest and with movement or coughing are obtained each day from either the patient’s medical record or by direct questioning by trial research staff at least once daily. The Pain Catastrophising Scale (PCS), which measures catastrophic thinking related to pain [27], and the NPQ are completed on day 2 or earlier if discharged. The incidence and nature of side effects in hospital that are considered possibly related to the study drug by the treating clinicians are recorded daily. Where there was discontinuation of study drug infusion, this is recorded with the reason and time when this occurs.

The incidence of any of the trial safety endpoints are recorded. In line with National Health and Medical Research Council (NHMRC) guidelines, serious adverse events (SAE), serious adverse reactions (SAR), and suspected unexpected serious adverse reactions (SUSAR) are reported to relevant trial governance authorities and the data and safety monitoring committee (DSMC) [28].

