Progression from acute to chronic pain after surgery and trauma involves sensitisation of central nervous system pathways, particularly at the level of the spinal cord, neuroinflammation, and spinal cord ‘wind-up’, with the N-methyl-D-aspartate (NMDA) receptor having a central role in this process [10–12]. Ketamine is a potent, non-selective NMDA antagonist which is commonly used as a second- or third-line agent for management of acute postoperative pain, because of its unique analgesic properties [13]. Ketamine administration can lead to psychomimetic or dissociative side effects in around 5% of surgical patients, including vivid dreams, hallucinations, and agitation, which limit dosage in a small proportion of patients in the postoperative setting [13].

The potential effect of ketamine on the development of CPSP is unclear. A Cochrane review examined the effect on CPSP incidence of several perioperative pharmacological interventions including gabapentinoids, membrane stabilisers, steroids, non-steroidal anti-inflammatories (NSAIDs), and NMDA receptor antagonists including nitrous oxide and ketamine. Across eight heterogeneous small studies totalling 914 patients, the authors found evidence of a potential benefit from intravenous (IV) ketamine, with an odds ratio (OR) versus placebo of 0.50 (95% confidence interval [CI] 0.33–0.76, *p* = 0.001) [14]. They cautioned that large trial data were lacking and needed. A more recent meta-analysis has reinforced this conclusion [15]. An extensive James Lind Alliance survey of 2000 health practitioners, patients, and public stakeholders in the UK nominated prevention of CPSP as a leading research priority for anaesthesia and perioperative medicine [16].

The ROCKet (*R*eduction *O*f *C*hronic post-surgical pain with *Ket*amine) trial is a large, multicentre, double-blind, parallel group, placebo-controlled, individually randomised superiority trial of the effect of perioperative IV ketamine on the incidence and severity of CPSP, measured at 3 months and 12 months following elective abdominal, thoracic, or major orthopaedic surgery. The trial is being conducted by the Australian and New Zealand College of Anaesthetists Clinical Trials Network (ANZCA CTN).

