Key inclusion criteria (see Table 2)	Consenting adult patients (≥ 18 years), ASA 1–3, undergoing elective or expedited surgery and anaesthesia with planned postoperative opioid analgesia and hospital stay of at least one postoperative night, for any one of the following: I. Abdominal surgery involving an expected skin incision at least 8cm in length, and including open inguinal herniorrhaphy II. Non-cardiac thoracic surgery, including mastectomy and breast reconstruction surgery and including all video-assisted thoracoscopic surgery (VATS) III. Hip, knee and shoulder joint arthroplasty and spinal surgery involving an expected skin incision at least 8 cm
Key exclusion criteria (see Table 2)	Age > 85 years, pregnancy, BMI > 45 kg/m^2^ or weight over 130 kg, ASA 4 or 5 Planned use of intra- or post-operative continuous IV lignocaine infusion Contraindications to IV ketamine administration
Study type	Interventional, phase III trial
	Primary purpose: prevention
	Allocation: randomised 1:1, stratified by (i) hospital, (ii) preoperative pain at surgical site Intervention model: parallel assignment Masking: double blind
Date of first enrolment	19 December 2017
Target sample size	4884
Recruitment status	Recruiting
Primary outcome	CPSP incidence at 3 months after index surgery
Key secondary outcomes	*Within 3 months after index surgery*: Acute postoperative pain severity (opioid consumption oral morphine equivalents, and mean, minimum and maximum NRS pain scores at rest and activity) on days 1–3 post-surgery (or until hospital discharge) Quality of recovery on day 1 using the QoR-15 Length of hospital stay defined as time from surgery start to hospital discharge Incidence of adverse/side effects related to the study drug during index hospital admission
	Severity of CPSP at 3 months after index surgery (mBPI) and neuropathic pain incidence (NPQ) Wellbeing and psychological distress at 3 months post-surgery (mBPI, EQ-5D-3L and K-10)
	*Within 12 months after index surgery*: CPSP at 12 months after index surgery; severity of CPSP at 12 months after index surgery (mBPI) and neuropathic pain incidence (NPQ) Wellbeing and psychological distress at 3 months post-surgery (mBPI, EQ-5D-3L and K-10)

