### Blinding

Trial participants, research, hospital pharmacy, medical and nursing staff, data collectors, trial statistician, and Steering, Operations and Endpoint Adjudication Committee (EAC) members are all blinded to trial group assignment until after completion of primary endpoint data collection and database finalisation and locking.

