### Safety endpoints and adverse event reporting and monitoring

Data on a range of adverse events among recruited patients is recorded during admission, at discharge from hospital, and at 3 months post-surgery, with complications classified according to body system (cardiovascular, respiratory, neurological, gastrointestinal, urinary system, musculoskeletal, metabolic, and haematological) and including sepsis/infection, prolongation of hospital admission, need for re-operation, hospital readmission, and death. Classification of severity follows the NHMRC Guidance on safety monitoring and reporting in clinical trials involving therapeutic goods (November 2016) [28] and Common Terminology Criteria for Adverse Events (CTCAE) [31]. An adverse event (AE) is one where the nature and severity are consistent with the current Product Information Brochure. Serious adverse events (SAEs) and suspected unexpected serious adverse reactions (SUSARs) are reported for events that are unexpected given the participant’s underlying condition, and in the opinion of the investigator, the event is possibly related to the ROCKet trial solution infusion. SAEs and SUSARs are reported to the trial coordinating centre who are responsible for informing the relevant ethics committees and the administering institution for the trial, within 24 h of the site investigators becoming aware of the event, using a dedicated reporting form. These reports are reviewed by the DSMC.

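### The key secondary side-effect outcome counts only events judged related to study drug, and that judgement is applied before recording; it should count events irrespective of attribution

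*Protocol article*

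**What the plan says.** Three places in the protocol article bear on this.

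- **Perioperative data collection** sets the collection rule for in-hospital side effects. Those entered are "side effects in hospital that are considered possibly related to the study drug by the treating clinicians are recorded daily". The same section says, separately, that trial safety endpoints are recorded, and attaches no relatedness condition to them.
- **Objectives, Table 1 (key secondary outcomes)** sets the outcome: "Incidence of adverse/side effects related to the study drug during index hospital admission". Relatedness is part of the definition.
- **Safety endpoints and adverse event reporting and monitoring** describes another stream: "Data on a range of adverse events among recruited patients is recorded during admission, at discharge from hospital, and at 3 months post-surgery". These are grouped under eight body systems, neurological and gastrointestinal among them, and the list also covers infection, prolonged admission, re-operation, readmission and death. No relatedness condition is stated for this recording. SAE and SUSAR reports do carry one: they are made where, "in the opinion of the investigator, the event is possibly related to the ROCKet trial solution infusion".

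Two further places matter for bias. **Blinding** lists "Trial participants, research, hospital pharmacy, medical and nursing staff, data collectors, trial statistician" among those blinded. **Background** says "Ketamine administration can lead to psychomimetic or dissociative side effects in around 5% of surgical patients", and names vivid dreams, hallucinations and agitation.

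**The concern.** Randomisation against placebo exists so that nobody has to decide, patient by patient, whether a drug caused an event. Here that decision comes first. A patient who is sedated, nauseated or agitated after surgery, and whose clinician blames the opioid or the anaesthetic, does not meet the rule for the side-effect record. Planned postoperative opioid analgesia is an inclusion criterion, so another explanation is nearly always to hand.

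Two things are at stake. One is the absolute frequency of side effects and the absolute difference between arms, which a reader needs when weighing a preventive drug offered across broad categories of major surgery. The other is the relative comparison. Ketamine has a recognisable profile, and the Intervention section expects clinicians to act when they suspect ketamine-induced side effects. Suspicion of allocation can therefore enter the relatedness judgement, even though clinicians are formally blinded.

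**Working it through.** The plan states no figure for this outcome, so there is nothing to reproduce. The arithmetic shows how the filter acts.

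**Inputs**

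- Patients per arm: n = 2442 (Sample size and study power).
- Assumed, because the documents give none: true risks of 5% or 20% in both arms (no effect), or 8% on ketamine versus 3% on placebo; attribution probabilities a from 0.25 to 1; two-sided alpha 0.05 for a side-effect comparison.

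**Formulas**, with p the true risk, K ketamine and P placebo

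- Recorded risk: r = p × a.
- Recorded risk ratio: (p_K / p_P) × (a_K / a_P).
- Recorded risk difference: p_K × a_K − p_P × a_P.

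**Step 1. Equal attribution, as blinding intends.** Take 8% versus 3%, a true risk ratio of 2.67 and a difference of 5 points.

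| a in both arms | Recorded risks | Risk ratio | Difference |
|---|---|---|---|
| 1 | 8.0% v 3.0% | 2.67 | 5.0 points |
| 0.5 | 4.0% v 1.5% | 2.67 | 2.5 points |
| 0.25 | 2.0% v 0.75% | 2.67 | 1.25 points |

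The ratio is untouched. Incidence and the difference are multiplied by a.

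**Step 2. Attribution that differs by arm, with no true effect.** The recorded ratio is then a_K / a_P. The chance of a significant spurious excess on ketamine is Φ(z), where z = [(r_K − r_P) − 1.96 × √(2r̄(1 − r̄)/n)] / √([r_K(1 − r_K) + r_P(1 − r_P)]/n) and r̄ is the mean of the two recorded risks.

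Example: true risk 20%, a = 0.60 v 0.50, recorded 12% v 10%. Both standard errors are about 0.00895, so z = (0.020 − 0.01755)/0.00895 = 0.27 and Φ(z) = 0.61.

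| a_K v a_P | Recorded ratio | Spurious excess, true risk 5% | Spurious excess, true risk 20% |
|---|---|---|---|
| 0.55 v 0.50 | 1.10 | 8% | 21% |
| 0.60 v 0.50 | 1.20 | 19% | 61% |
| 0.75 v 0.50 | 1.50 | 71% | >99% |

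Without any bias, the chance of a significant excess in that direction would be 2.5%.

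**Step 3. Does the general adverse-event recording supply the outcome?**

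- It has no stated relatedness condition, and its body systems include neurological and gastrointestinal, so some of these events may be in it.
- It describes complications and lists no psychiatric or psychomimetic category. The article does not say whether vivid dreams or dysphoria fall under neurological.
- The same section then defines an adverse event by consistency with the product information, which is a reference to the drug.
- Nothing links this recording to the Table 1 outcome, which keeps its own relatedness condition.
- Delirium assessment (Sub-studies) covers only patients aged 65 or over in a sub-study.

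The unfiltered recording may therefore hold part of what is needed, but the article does not connect it to the outcome.

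**The case against.** The strongest reply is that unfiltered recording already exists. The safety section records a range of adverse events during admission, at discharge and at 3 months, and the full protocol or case report form, which is not shown, may contain a symptom checklist. This stands in part. A reader might infer from the collection rule that side effects are captured only when a clinician attributes them to study drug and are otherwise lost; the documents do not support that. They do support the narrower point, because a checklist would not alter an outcome that Table 1 defines by relatedness.

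Second, the judges are blinded, the threshold is only a possible relation, and an event must happen before it can be recorded. This also stands. A reader might infer that the outcome measures guesses about allocation and not events; that goes too far. A biased risk ratio requires attribution to differ by arm. The Background and Intervention sections make that possible but do not show that it happens. Large assumed gaps in attribution can produce striking ratios, but such ratios come wholly from the assumption. With low but equal attribution, events are lost and the ratio is unchanged.

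Third, recruitment began in December 2017 and was expected to finish in the first half of 2025, so a new checklist would reach few patients. That is correct, and it moves the remedy mainly to the outcome definition and analysis.

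**Conclusion.** The concern holds in a limited form. The causality filter is a written rule, present in both the collection instruction and the outcome definition; it is not inferred from silence. Followed as written, it understates absolute incidence and the risk difference by the attribution probability, even under perfect blinding. It also leaves the risk ratio open to bias if attribution differs by arm, in proportion to a_K / a_P. The first effect follows whenever attribution is incomplete. The second is a risk, not an established fact. The sizes shown rest on assumed event risks and attribution rates, for which the documents give no values. This affects a key secondary outcome and the weighing of harm against benefit; it does not affect the primary endpoint.

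**What to change.** Before unblinding, while the detailed statistical analysis plan is still to be written:

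1. Redefine the side-effect outcome in Table 1 as the incidence of in-hospital events irrespective of attribution, using the adverse-event recording in the safety section wherever it captures them.
2. Report clinician-attributed side effects as a secondary analysis, labelled as attributed.
3. Reconcile Table 1, Perioperative data collection and the safety section. State which recording supplies the outcome, and whether psychomimetic events such as hallucinations, vivid dreams and dysphoria are within it.
4. For patients still to be enrolled, record occurrence at the daily research visits that already take place, with causality as a separate field.

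The cost is a wording change, a documented change of definition made while blinded, and a small case-report-form change. Event counts will be higher in both arms. Any newly collected items will exist for late enrolees only and should be reported separately. Where the existing recording turns out not to contain psychomimetic events for earlier patients, only the attributed version is available for them, and the report should say so.

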### Post-operative follow-up at 3 and 12 months

The protocol for collection of data on CPSP is designed to meet the 6 core domain requirements set out by the recommendations of the Initiative on Methods, Measurement, and Pain Assessment in Clinical Trials (IMMPACT) [29, 30]. These are (1) pain assessment, (2) physical functioning, (3) emotional functioning, (4) participant ratings of improvement and satisfaction with treatment, (5) symptoms and adverse events, and (6) participant disposition.

Following review of the patient’s hospital medical history, research staff contact the patient by phone at 3 and 12 months after surgery. A structured interview is then conducted to determine the incidence, severity, and nature of CPSP reported by the patient. Figure 1 summarises the trial process and timeline.

**Fig. 1 Fig1:**
[figure not shown]
Trial process and timeline summary

### Primary endpoint: CPSP at 3 months

Patients are asked whether they have experienced pain in the area of the index surgery in the previous week. If so, details including free text description of the pain by the patient, and of any difference from preoperative pain if it was present, are recorded, and the adapted mBPI-sf and NPQ questionnaires are administered.

CPSP is defined as pain in the area of the index surgery in the previous week which either was not present preoperatively or is different in site, nature, or intensity (NRS score ≥ 2/10 difference) to any pain present at the site prior to surgery. Pain reported at interview by the patient and its recorded details are subsequently adjudicated to determine whether they meet this definition, by two members of the treatment-blinded EAC, which consists of pain medicine specialists who are all Fellows of the Facult*y* of Pain Medicine of ANZCA (ANZCA FPM). Where these two members disagree on the outcome for a given patient, further review by a third member is done as a ‘tiebreak’.

Secondary analyses will measure the incidence and treatment effect on moderate (mean NRS score ≥ 3/10 and < 5/10) and severe (mean NRS ≥ 5/10) CPSP. CPSP incidence and severity and ketamine treatment effect at 12 months will be reported as part of a subsequent long-term follow-up study.

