### Secondary and exploratory endpoints

The effect of ketamine on indices of acute postoperative pain severity (opioid consumption measured as oral morphine equivalents, and NRS pain scores) on the first three postoperative days (or until hospital discharge) will be assessed. Quality of recovery in the two trial treatment arms will be compared using the QoR-15 on day 1 post-surgery.

Measures of wellbeing and psychological distress using the EQ-5D-3L and K-10 are collected in all patients prior to surgery and at 3 and 12 months post-surgery. The relationship of change from baseline to 3 and 12 months post-surgery in these variables will be examined with respect to trial treatment effect.

Patients who deny the presence of pain at follow-up are also asked if they have experienced ‘discomfort’ in the area of the index surgery in the previous week, followed by a similar pathway of questions. This pursues a secondary hypothesis that some patients may experience chronic symptoms which they may not identify as pain, particularly neuropathic symptoms, but which may adversely affect quality of life. The incidence of, and treatment effect on, this novel endpoint will be investigated as secondary trial outcomes in parallel to CPSP and reported separately.

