### Statistical analysis

A detailed statistical analysis plan will be developed prior to unblinding of the data collected up to 3 months after surgery. In what follows, the analysis plan using data up to and including the primary endpoint data is described. A separate plan will be written before unblinding for the data collected up to 12 months post-surgery.

The analysis will include all randomised patients, excluding patients who had their surgery cancelled post-randomisation and did not return later for their planned surgery. For the analysis of the efficacy outcomes, patients will be reported and analysed according to their randomised study arm (i.e. ‘as randomised’). For the analysis of safety outcomes, patient data will be reported and analysed according to the intervention received (i.e. ‘as treated’), whereby those who did not receive at least one study treatment will be excluded from the analysis.

The primary estimand for the ROCKet trial is defined according to the addendum to the ICH E9 on estimands and sensitivity analysis in clinical trials [32]. The trial aims to answer the specific research question: does IV ketamine, given immediately prior to and for up to 72 h following surgical incision, compared to placebo, reduce CPSP at 3 months after surgery, measured by the relative difference in the incidence/risk (i.e. RR) of CPSP at 3 months after surgery between treatment arms, regardless of the post-randomisation (intercurrent) events listed below, while assigning the patients who died to have CPSP at 3 months?

Primary estimand attributes are:Treatment: IV ketamine, given immediately prior to and for up to 72 h following surgical incision, compared to placebo, allocation by randomisationPopulation: consenting adult patients presenting for elective or expedited surgery under anaesthesia for a variety of major surgeries associated with CPSPVariable: CPSP at 3 months post-surgeryIntercurrent events: not receiving trial solution during surgery will be handled using a treatment policy strategy, while death (expected incidence to be around 0.5% at 3 months) will be handled using a composite strategy by assigning the patients who died to have CPSP at 3 monthsPopulation level summary: relative difference in the incidence/risk (i.e. RR) of CPSP at 3 months after surgery between treatment arms (IV ketamine versus placebo)

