The primary outcome of CPSP (yes/no) at 3 months after surgery will be analysed using a binomial log-linear regression model, with the placebo group as the reference, and in the model site, presence or absence of preoperative pain in the area of the surgery (stratification factors), and treatment. The primary hypothesis will be evaluated by obtaining the estimate of the RR for treatment and a 95.1% confidence interval (two-sided *α* = 0.049).

Binary secondary effectiveness outcomes will be analysed similar to the primary outcome and targeting a similar primary estimand, and for continuous secondary effectiveness outcomes, a linear regression model will be fitted with a model specification similar to that of the primary outcome. Sensitivity analysis will be conducted adjusting the model for pre-specified baseline covariates. Supplementary analysis targeting a different estimand with a different strategy for handling the intercurrent event of death will also be performed.

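### Moderate CPSP as a closed band, and discomfort asked only of patients without pain, have no fixed direction of benefit, so either risk ratio can exceed 1 when ketamine works

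*Protocol article*

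**What the plan says.** Under Primary endpoint: CPSP at 3 months, the article says "Secondary analyses will measure the incidence and treatment effect on moderate" and severe CPSP. The full definition is "moderate (mean NRS score ≥ 3/10 and < 5/10) and severe (mean NRS ≥ 5/10) CPSP". The two bands do not overlap, and moderate has an upper limit.

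Under Secondary and exploratory endpoints, discomfort in the area of surgery has a gate: "Patients who deny the presence of pain at follow-up are also asked if they have experienced" it. The plan for this outcome is: "The incidence of, and treatment effect on, this novel endpoint will be investigated as secondary trial outcomes in parallel to CPSP and reported separately".

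The analysis is set under Statistical analysis: "Binary secondary effectiveness outcomes will be analysed similar to the primary outcome and targeting a similar primary estimand". The primary analysis is a binomial log-linear model giving an RR of ketamine against placebo, so a binary secondary outcome also yields an RR. The article gives no expected incidence for moderate CPSP, severe CPSP or discomfort.

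**The concern.** An RR for a yes/no outcome is readable when every improvement moves a patient from event to non-event. That does not hold here.

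- **Moderate band.** A patient whose mean NRS would have been 6 and is 4 on ketamine becomes a moderate event. One who would have been 4 and is 2 stops being an event. Both have improved, but they move the RR in opposite directions. A patient who worsens from 4 to 6 also lowers the moderate count.
- **Discomfort.** The group that is asked is defined after randomisation by an outcome that ketamine is meant to change. A patient freed of pain enters that group and can become a discomfort event only because the pain has gone.

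An RR above 1 on either outcome is therefore not evidence of harm, and an RR below 1 is not by itself evidence of benefit. At stake is the reading of two planned secondary results, not the primary conclusion.

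**Working it through.** **Inputs from the article.** The 3-month design assumption is 23.75% on placebo against 20.25%, described as an RR of 0.85, with two-sided alpha 0.049, 4884 patients and about 6% loss. These figures are coherent: 20.25/23.75 = 0.853, the mean of the two rates is 22%, and 4884 × 0.94/2 = 2295 per arm gives a power of 81.5%, in line with the stated 80% or more.

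**Assumptions.** The article gives no severity split, so 50/30/20 (mild/moderate/severe) of 23.75% is assumed first: mild 11.875%, moderate M = 7.125%, severe S = 4.75%. Other splits follow. Discomfort among pain-free patients is assumed to be 10% or 20%.

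**Moderate band.** Let s be the share of a band that moves down one step.

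1. Only severe patients improve: RR = (M + sS)/M = 1 + s × 4.75/7.125.
2. Both bands improve by the same share: RR = (M(1 − s) + sS)/M = 1 − s + s × S/M, which is 1 − s/3 for this split.
3. Equal proportional prevention in each band: RR = 0.85.

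| s | Severe only | Both bands |
|---|---|---|
| 0.10 | 1.07 | 0.97 |
| 0.20 | 1.13 | 0.93 |
| 0.30 | 1.20 | 0.90 |

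In the severe-only column nobody is worse off, severe CPSP falls, and the RR for mean NRS ≥3 stays at 1.00.

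The second formula exceeds 1 only when S > M. With s = 0.15:

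| Split (mild/moderate/severe) | Moderate RR |
|---|---|
| 50/30/20 | 0.95 |
| 40/35/25 | 0.96 |
| 30/30/40 | 1.05 |
| 20/30/50 | 1.10 |

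A latent normal severity (SD 2; mean 2.5, 3.5, 4, 4.5 or 5) shifted down by 0.5 or 1 point shows the same. The RR for the 3 to <5 band runs from 0.63 to 1.12, while the RR for ≥3 stays between 0.57 and 0.92, and severe falls in every case.

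**Discomfort, over all randomised patients.** Let P be pain on placebo, d discomfort among the pain-free, q discomfort among patients freed of pain, and r the direct effect of ketamine on discomfort in patients who would be pain-free anyway. Then

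RR = [(1 − P)dr + 0.15Pq] / [(1 − P)d].

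The article gives CPSP incidence, not the incidence of any reported pain, so P = 23.75% is a stand-in and P = 35% is tried as well.

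- P = 23.75%, q = d, r = 1: pain-free patients rise from 76.25% to 1 − 0.85 × 0.2375 = 79.81%, so RR = 79.81/76.25 = 1.05 whether d is 10% or 20%.
- P = 23.75%, r = 1, q = 50%: RR 1.23 (d = 10%) or 1.12 (d = 20%). With q = 100%: 1.47 or 1.23.
- P = 35%, r = 1: RR from 1.08 to 1.81.
- r = 0.85: RR from 0.90 to 1.66 over all these cases, so it can fall.

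Using only the patients who were asked as denominator gives RR = 1.00 in the first case, but up to 1.40 at P = 23.75% (d = 10%, q = 100%, r = 1). It also compares groups selected by a post-randomisation outcome.

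**Pain or discomfort instead.** With P = 23.75%, d = 10% and r = 1, placebo is 0.2375 + 0.07625 = 0.31375. On ketamine, q = 10% gives 0.201875 + 0.0798125 = 0.2817 (RR 0.90). With q = 100% it gives 0.201875 + 0.111875 = 0.31375 (RR 1.00). The RR does not rise above 1 when patients only move from pain to discomfort or to neither.

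**The case against.** Moderate and severe are planned together, beside the primary analysis and a key secondary outcome on CPSP severity (mBPI), so a reader can add the two incidences to obtain NRS ≥3. Discomfort is a novel outcome for a separate hypothesis, asking only those who deny pain follows from its definition, and nothing in the article says a rise would be called harm. Full details may lie in an analysis plan that is not shown.

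Much of this stands, and it keeps the point small. Crude incidences can be added. An adjusted, imputed RR and its interval for NRS ≥3 cannot be obtained from two separate band models. The band limits and the discomfort gate are already fixed in the text, with a treatment effect planned on each, so they are not merely left to a later plan.

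Two stronger readings are tempting, and the document supports neither.

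- **That both outcomes rise when ketamine works.** The calculations contradict this as a general claim. Moderate falls under proportional prevention and under an equal one-step shift with the first split, and discomfort falls if ketamine reduces it enough. The 1.07 to 1.20 range needs an effect confined to severe patients.
- **That each death counts as both moderate and severe.** The primary estimand uses a "composite strategy by assigning the patients who died to have CPSP" at 3 months and names no severity band. Binary secondary outcomes target only a similar estimand. How deaths are coded by severity is a detail that an analysis plan can settle. At the stated rate ("expected incidence to be around 0.5% at 3 months"), it concerns 0.005 × 4884, or about 24 patients.

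**Conclusion.** The point holds in limited form. The article plans treatment effects on two secondary outcomes without a fixed direction of benefit, and either RR can exceed 1 when patients only improve. For the moderate band, plausible patterns of benefit give RRs from 0.63 to 1.20 in the single-step and latent-shift scenarios tried. For discomfort with no direct drug effect, the RR over all randomised patients is 1.05 to 1.81; with a 15% direct reduction it is 0.90 to 1.66.

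All of these rest on assumed severity splits, latent means and discomfort rates. They show that the sign is undetermined and do not predict the result. No error in the handling of deaths is shown. The matter is worth correcting because it is cheap, but it is confined to secondary outcomes.

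**What to change.** 1. Estimate severity effects on cumulative thresholds over all randomised patients: CPSP with mean NRS ≥3, and CPSP with mean NRS ≥5. Show the 3 to <5 band by arm descriptively.
2. Estimate the treatment effect on pain or discomfort over all randomised patients, beside the descriptive incidence of discomfort alone. State that pain here means pain reported at interview, since that report decides who is asked about discomfort.
3. State how a death is coded at each threshold. An event at both ≥3 and ≥5 involves no contradiction, because the second outcome is contained in the first.

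The cost is wording in the analysis plan and recoding of variables already collected; no new data and no change to the sample size. The article says the detailed plan is to be developed before the 3-month data are unblinded, so the change can be made without knowledge of results. The downside is that moderate-only and discomfort-only contrasts lose their separate inferential RR. The combined outcome also counts patients whose reported pain is not adjudicated as CPSP, which may dilute its contrast.
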